## 5. Study aims and endpoints

As shown in table 1, the study was planned with 1 primary endpoint, 7 secondary endpoints, and 1 ancillary endpoint. In addition, the protocol states that:

"We will undertake a planned subanalysis of patients observed early during baseline (first 2 months) and compare them to patients undergoing surgery during the final stage of the study (last 2 months) after implementation of the program has had time to take effect to assess primary and secondary outcomes." (p.9)

Table 5 lists the original aims along with two aims we added after the publication of the protocol. The first is a composite outcome of complications after caesarean section, in which we include surgical infection, maternal mortality, and neonatal mortality (Aim 5). The second is Aim 6, an analysis aimed at showing the relationship between perioperative infection prevention practices and our primary outcome, infection after caesarean section.

Finally, we plan to pursue the subanalysis stated in our protocol in a future publication. This subanalysis focuses on changes in compliance with infection prevention practices across the study in relation to secular, temporal trends. We will demonstrate the relationship between compliance and secular and temporal trends by creating a graph on compliance with infection prevention practices at four points in time: the first two months of data collection vs the final two months of the intervention and the two months prior to the start of the intervention vs the two months immediately following the intervention.

In Table 5 we also list whether each endpoint will be addressed in this analysis or in future publications. For ease of reference, we renumber the aims that are addressed in this SAP and will refer to them by this renumbering hereafter.

Table 5: Plan for addressing aims in this or future analyses

| Aim     | Endpoint | Plan | Numbering in this SAP |
|---------|----------|------|-----------------------|
| Primary |          |      |                       |

|                                                                     |                                                |                           |       |
|---------------------------------------------------------------------|------------------------------------------------|---------------------------|-------|
| Infection reduction in CS                                           | Surgical infection                             | Included in this analysis | Aim 1 |
| Secondary                                                           |                                                |                           |       |
| Improved compliance with infection prevention practices             | Compliance score                               | Included in this analysis | Aim 2 |
| Infection reduction in Ob/Gyn cases                                 | Surgical infection                             | Future publication        | -     |
| Reduction in unplanned reoperation                                  | Reoperation                                    | Future publication        | -     |
| Reduced length of stay                                              | Length of stay                                 | Future publication        | -     |
| Reduced maternal postoperative mortality                            | Maternal mortality                             | Included in this analysis | Aim 3 |
| Reduced postoperative mortality                                     | Postoperative mortality                        | Future publication        | -     |
| Reduced neonatal mortality                                          | Neonatal mortality                             | Included in this analysis | Aim 4 |
| Ancillary                                                           |                                                |                           |       |
| Assessment of readiness for QI generally and CLEAN-CS in particular | Facility readiness score                       | Future publication        | -     |
| Additional (not pre-specified)                                      |                                                |                           |       |
| Composite outcome                                                   | SSI, maternal mortality, or neonatal mortality | Included in this analysis | Aim 5 |
| Relate compliance to outcomes                                       | Compliance, surgical infection                 | Included in this analysis | Aim 6 |
| Sub analysis                                                        |                                                |                           |       |
| Subanalysis of 2 months immediately pre and post implementation     | Compliance score                               | Future publication        | -     |

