## **Study Design**

The impact of the CS-tailored Clean Cut program will be tested through a stepped-wedge study design at 10 hospitals over the course of 18 months followed by data analysis and interpretation. These hospitals will start by collecting inpatient and outpatient outcomes on all patients undergoing CS prior to implementation (phases 1 and 2 of Clean Cut outlined above). Over the course of 10 months, 2 hospitals at a time will begin implementing phase 3 of Clean Cut at 2-month intervals. They start by

---

Birkmeyer JD, et al. Measuring the quality of surgical care: structure, process, or outcomes? *JACS* 2004;198(4):626-632

Saluja S, et al. Quality of essential surgical care in low- and middle-income countries: a systematic review of the literature. *Int J Qual Health Care* 2019;31(3):166-172

Allegranzi B, et al. A multimodal infection control and patient safety intervention to reduce surgical site infections in Africa: a multicentre, before–after, cohort study. *Lancet Infect Dis* 2018;18:507-515

Forrester JA, et al. Developing process maps as a tool for a surgical IP quality improvement initiative in resource-constrained settings. *J Am Coll Surg* 2018;226(6):1103-16e3

assembling a multidisciplinary improvement team, undergoing team training on WHO Surgical Safety Checklist use and implementation, and gathering compliance information about intraoperative safety practices. The initiation of Clean Cut will also involve creating facility-specific process maps of each critical perioperative practice. Once these process maps and compliance data are complete, usually after 2-4 weeks, the team establishes an adaptive, facility-driven improvement plan based on process gaps and barriers to best practice. This is initially facilitated by Lifebox, but soon transitions to teams that have already implemented Clean Cut. They identify improvement opportunities by reviewing process mapping data, their bespoke surgical safety checklist, and identified compliance shortfalls, and craft an improvement plan aimed at removing barriers to compliance. The team will review their hospital-specific data and patient outcomes on a monthly basis for the remainder of the six-month implementation period. For the remainder of the 18-month time period, the teams will continue to follow patient outcomes but will follow compliance information only at their own discretion.

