**Figure 2: Monthly recruitment rates needed to detect selected outcome proportions**

[figure not shown]

**Analysis:** We will conduct pre/post analyses using the statistical approach recommended by Hemming with our planned assessment controlling for risk factors and other demographic and procedure variables listed below that are known to affect infection rates. We will compare patient demographics pre and post intervention as well to evaluate overall matching of patients in each part of the study. We will evaluate compliance individually and in an all-or-none manner as previously described in our Clean Cut pilot work. We will undertake a planned subanalysis of patients observed early during baseline (first two months) and compare them to patients undergoing surgery during the

final stage of the study (last two months) after implementation of the program has had time to take effect to assess primary and secondary outcomes.

As we are interested not only in the primary outcome of surgical infection but also in process improvements and the implementation strategies and support that can lead to effective compliance with best practices, we will not conduct any interim analyses. The purpose of an interim analysis is to assess the study for benefit, futility or harm. We believe that neither benefit nor futility would be readily observable at an interim analysis given the implementation strategy and approach; furthermore, even if we were able to assess benefit or futility we would want to continue the trial to fully study the mechanisms of implementation. Regarding an assessment of harm, if such an outcome were noted we believe this would most likely be due to detection bias with improving ability to capture complications as the study progressed, and we would want to let the study play out to mitigate this detection bias over time.

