### 3.2. As executed

Our protocol made allowance for difficulties that may arise in the field:

“Given the current pandemic as well as potential civil unrest in Ethiopia, there is the potential for unanticipated challenges to implementing the protocol as described. While every attempt will be made to maintain participation of all sites, the loss of one or more sites is a distinct possibility. Recruitment of patients may also be affected by patient volumes, supply shortages, or facility closures. Given this, we will allow each site to collect up to 92 patients per month if they are able in case of the loss of a facility in a cluster. In the case where one facility in a cluster is no longer participating in the study, we will allow the other facility to increase data collection up to 150 cases per month, if feasible and the volume allows, and adjust our comparative calculations accordingly.” (p.11)

Data collection for the trial occurred from August 2021 to January 2023. Although we were able to successfully launch the intervention in all five cohorts and observe operations for over ten thousand patients, we did encounter two main fieldwork challenges that may affect the analysis plan:

1. One hospital did not participate

One hospital was unable to carry out the data collection required to participate in the study. After several attempts to begin data collection, the hospital and study team agreed to proceed without that hospital. As specified in the protocol, we did not replace that hospital, but the other hospital in its cohort was high-recruiting and was able to meet the expected patient enrollment for the cluster.

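### The first-two-months versus last-two-months subanalysis is an uncontrolled before-after contrast that cannot separate the program from calendar time, and no month-adjusted model is named for it

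*Combined protocol and SAP*

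**What the plan says.** The protocol's Analysis paragraph states: "We will undertake a planned subanalysis of patients observed early during baseline (first two months) and compare them to patients undergoing surgery during the"; the sentence goes on to name the last two months of the trial. The reason given is that this stage comes "after implementation of the program has had time to take effect to assess primary and secondary outcomes".

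SAP section 5 repeats that sentence and then says "we plan to pursue the subanalysis stated in our protocol in a future publication". It gives the purpose as follows: "We will demonstrate the relationship between compliance and secular and temporal trends by creating a graph on compliance with infection prevention practices". The four points are "the first two months of data collection vs the final two months of the intervention and the two months prior to the start of the"; the last window named there is the one before launch, and it is set against the two months right after launch. Compliance is the only outcome mentioned. No model, test or estimate is named, and the text does not say whether the points are pooled over cohorts.

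Other places bear on this:

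- SAP Table 5 lists the subanalysis as the pair of windows around launch only.
- The SAP table of contents lists an Aim 8 on first and last months, but the body has no such section.
- The main model in SAP section 7.1 carries a fixed effect for each of 18 calendar months.
- The protocol's Study Design section has teams review their data monthly "for the remainder of the six-month implementation period". After that, outcomes are still followed, but compliance is tracked only if the team chooses to.

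**The concern.** The strength of a stepped wedge is that, for much of the trial, some hospitals have launched and others have not in the same month. A comparison of the two ends of the trial uses none of that. If compliance rose for other reasons, such as being observed or wider national work on surgical quality, the rise would sit inside the first-versus-last difference and could be taken for a program effect.

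The second pair of windows is also before-after. If the two pairs differ, a reader could call the gap a secular trend when it may be the program maturing. The protocol's form also covers the primary outcome, so the same contrast could be run on infections.

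**Working it through.** **1. Inputs.** SAP section 3.2: "Data collection for the trial occurred from August 2021 to January 2023", which is 18 months. The launch dates are in SAP Table 2. The run-in without data, four to six weeks, is in SAP section 3.2. The documents give no sample size or effect for this subanalysis. As a check that Table 2 has been read correctly: control 230 + 948 + 959 + 2,002 + 1,576 = 5,715; intervention 772 + 1,704 + 975 + 1,087 + 413 = 4,951; total 10,666, a 54%/46% split as stated.

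**2. Status in the two end windows.** Read as calendar windows, these are August–September 2021 and December 2022–January 2023. The first launch was 28 December 2021 and the last 13 September 2022. So 5 of 5 cohorts are control in the first window and 5 of 5 are intervention in the last. The windows share no calendar month of the year. Their midpoints, about 1 September 2021 and 1 January 2023, are 16 months apart.

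**3. Can adjustment rescue the pair?** Take one column per cohort (5), month contrasts (3) and intervention (1), making 9 columns. The rank is 8, and it is still 8 without the intervention column, because intervention equals the sum of the two last-window month indicators. No adjustment for month can separate them.

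**4. Do the added windows help?** Launches are rounded to study months 6, 8, 10, 12 and 14, with the post-launch window starting 0, 1 or 2 months after launch. All four windows with cohort and month terms then give rank 21 of 21 (gap 0) or 22 of 22 (gap 1 or 2), so the effect is estimable in a month-adjusted model. The full wedge gives 23 of 23. Full rank says nothing about precision.

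The reason is overlap. If run-in starts at launch, each cohort's post-launch window coincides with part of the next cohort's pre-launch window:

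- Cohorts 1 and 2: 25 January–8 February to 1 March 2022, 21 to 35 days
- Cohorts 2 and 3: 29 March–12 April to 9 May 2022, 27 to 41 days
- Cohorts 3 and 4: 6–20 June to 11 July 2022, 21 to 35 days
- Cohorts 4 and 5: 8–22 August to 13 September 2022, 22 to 36 days

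That is about 3 to 6 weeks at each step.

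**5. What the whole wedge offers.** From 28 December 2021 to 13 September 2022 is 259 days, or 259 / 30.44 = 8.5 months, with launched and unlaunched cohorts side by side. Allowing for cohort 1's run-in leaves 217 to 231 days, or 7.1 to 7.6 months. Cohort 5 alone supplies 408 / 30.44 = 13.4 months of control time (1,576 patients).

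**6. Make-up of the last window.** Months since launch = days / 30.44:

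| Cohort | Launch | At 1 Dec 2022 | At 31 Jan 2023 | Six months from launch |
|---|---|---|---|---|
| 1 | 28 Dec 2021 | 11.1 | 13.1 | 28 Jun 2022 |
| 2 | 1 Mar 2022 | 9.0 | 11.0 | 1 Sep 2022 |
| 3 | 9 May 2022 | 6.8 | 8.8 | 9 Nov 2022 |
| 4 | 11 Jul 2022 | 4.7 | 6.7 | 11 Jan 2023 |
| 5 | 13 Sep 2022 | 2.6 | 4.6 | 13 Mar 2023 |

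Counted from launch, cohorts 1 to 3 are past six months for the whole window, and cohort 4 from 11 January 2023. Under the protocol their compliance data are then discretionary.

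**7. Size of the possible error.** The documents give no secular trend, so the rates here are assumed. With no program effect at all, a steady rise of r points per month gives a difference of 16 × r: 4 points at r = 0.25, 8 at r = 0.5, 16 at r = 1.

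**8. If infections were compared.** Auditors called from September 2022 to March 2023 (SAP section 4.1). First-window patients were then at least about 11 months from surgery and last-window patients at most about 4, so length of recall would move with the contrast as well.

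**The case against.** The strongest reply is that two of the four points are untreated: the first two months and the two months before launch. The change between them is a trend within control hospitals, and for cohort 5 it spans nearly a year. Together with the overlaps in step 4, this means the data in the four windows can inform on a secular trend. A reader might infer that the four points cannot serve their purpose at all. The documents do not support that. What is lost depends on pooling over cohorts, which section 5 neither states nor rules out.

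Second, no trial conclusion rests on the graph. It is descriptive and deferred, and the compliance effect is Aim 2, which uses the model with month effects. This stands in full.

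Third, a reader might infer that the last window contradicts the protocol because cohort 5, and cohort 4 for most of the window, had not completed six months. Neither document defines taking effect as six completed months. The protocol has the improvement plan following process mapping that usually takes 2–4 weeks, and the SAP's settling-in period is four to six weeks; cohort 5 is past both. What remains is narrower: the window averages over very unequal times since launch.

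None of this answers the point about the first-versus-last pair taken alone.

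**Conclusion.** The concern holds for the first-versus-last pair. It has no concurrent control, and the program cannot be separated from about 16 months of calendar time or from season, with or without month adjustment. For the four-point graph the finding is weaker: usable control information exists in the windows, but points pooled over cohorts would hide it, and no month-adjusted model is named to recover it. The last window mixes cohorts from 2.6 to 13.1 months after launch, and part of its compliance data is discretionary under the protocol.

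The consequence is confined to this subanalysis. It gives no ground for doubting the inference in SAP Aims 1 to 6. The conclusion assumes calendar windows. Hospital-level start dates cannot be read from Table 2; a late-starting hospital could have a different season mismatch, but its first window would still be control and its last still intervention. The 4-to-16-point range is an illustration, not an estimate.

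**What to change.** 1. Plot compliance by calendar month with separate series for launched and not-yet-launched cohorts, or one series per cohort. Read the secular trend from the not-yet-launched series up to 13 September 2022.
2. Estimate any effect of time since launch in the stepped-wedge model with month effects.
3. If first-versus-last is kept, label it an uncontrolled before-after description, draw no effect conclusion from it, and report completeness of compliance data by cohort for the last window. Do not limit it to cohorts 1 to 3: those are the cohorts whose compliance data are discretionary throughout that window, so the restriction could add selection.
4. Reconcile the protocol's Analysis paragraph (first versus last, primary and secondary outcomes), the SAP contents (an Aim 8 with no section), SAP section 5 (four windows, compliance only) and Table 5 (launch-adjacent windows only).

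The cost is a paragraph of SAP text and a different graph from data already collected. The downsides are a less striking picture than first-versus-last, and a not-yet-launched series that shrinks to cohort 5 after 11 July 2022, so its hospital mix changes, and then ends. Plotting by cohort makes that visible.

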## 6. Study populations

The aims addressed in this SAP require two study populations, defined as:

### *CS population with follow-up*

All CS patients enrolled in the study who have complete 30-day follow-up data collected by the auditors.

### *Total intraoperative population*

All patients enrolled in the study who had data collected on compliance with perioperative infection prevention practices in the operating room (all operations, regardless of follow-up.)

## 7. General statistical considerations

### 7.1. Modeling

As stated in our protocol, we will use the statistical approach recommended by Hemming and colleagues. To estimate how the intervention is correlated with outcomes, we will fit a mixed effects logistic regression model of the form:

$$Outcome_{ij} = \beta_0 + \beta_1 Month + \beta_2 Intervention + \beta_x X + \mu_i + \varepsilon_{ij}$$

Where:

|                       |                                                                                                                                                     |
|-----------------------|-----------------------------------------------------------------------------------------------------------------------------------------------------|
| Outcome ij | Binary variable for the j th patient in the i th cohort, where 1 = had the adverse outcome, and 0 = did not have the outcome. |
| Month                 | Fixed categorical variable with 18 levels, one for each month. Reference category will be either the first or last month of the study.              |
| Intervention          | Fixed binary variable, where 1 = procedure occurred under intervention condition, 0 = procedure occurred under control condition.                   |
| X                     | Vector of fixed demographic and clinical controls                                                                                                   |
| β 0-x      | Set of regression coefficients                                                                                                                      |
| μ i        | Random effect for cohort                                                                                                                            |
| ε ij       | Error term for the j th patient in the i th cohort                                                                            |

Since this is a cross sectional design (no repeated measures on patients over time), we will not need to account for patient-level correlation over time. The random effect for cohort will account for the within-cluster variance, assuming one shared ICC. We will consider adding a random cohort-by-month interaction term, which would allow for different within-period and between-period ICCs.

Our estimate of interest is  $\exp(\beta_2)$ , the exponentiated coefficient for the intervention period, which will express the odds ratio (OR) of having the outcome after the intervention started versus beforehand.

Note: In our pilot work, we modeled the surgical infection outcome with a modified Poisson regression, specifying a Poisson distribution for the binary outcome with a log link and robust

error estimation. This method directly estimates relative risks (RR) rather than ORs, which can overestimate RRs when the baseline risk is high. However, in this case we believe the baseline risks are low enough as to not require this correction. Further, the pilot was an uncontrolled pre-post study, and for the current analysis we will adhere to the standard logistic mixed effects approach for randomized stepped wedge trials, as stated in our protocol.

Because we cannot tell with complete certainty the differences between hospitals or the effects of sociopolitical factors in Ethiopia during this time, we will also model our primary outcome using generalized estimating equation (GEE) as a sensitivity analysis to assess whether any alternative model would better assess the outcomes of this study. While we do not necessarily anticipate large differences in results between models, if we do find differences in magnitude or significance of the effect of the intervention in a GEE framework versus mixed effects, we will pursue further analysis to dissect what may be driving those differences.

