## **Program Evidence**

Lifebox developed Clean Cut as a multimodal, adaptive, checklist-based improvement program following an extensive consultation with providers and practitioners from around the world who identified surgical infections as a major source of preventable surgical morbidity and mortality. The program was introduced in Ethiopia, initially in conjunction with the Surgical Society of Ethiopia and then through partnerships with the FMOH. Clean Cut was first evaluated at Jimma University Specialized Hospital in 2016, with the pilot work extending to five initial hospitals where we prospectively collected compliance data from 2213 operations (374 during baseline assessment and 1839 following implementation of process improvements) in 2202 patients with follow up in 2159 patients (98.0%). At baseline, perioperative teams only complied with an average of 2.9 of the six critical perioperative infection prevention standards; following process improvement changes, compliance rose to 4.5 ( $p < 0.001$ ). The relative risk of surgical infections following Clean Cut implementation was 0.65 (95% CI 0.43-0.99;  $p = 0.043$ ). Improved compliance with standards reduced the risk of postoperative infection by 46% (RR 0.54 for adherence score 3-6 vs 0-2; 95% CI 0.30-0.97;  $p = 0.038$ ).

Since then the program has been implemented in 11 hospitals and has benefitted an estimated 34,000 patients. In our preliminary, unpublished analyses of 8 hospitals with completed data, we have prospectively collected compliance data from 2905 operations, of which 1133 (39%) were CS or hysterectomy, with an average monthly volume of 27 obstetric operations per facility. Of the total, 2692 patients (92.7%) had outcomes follow-up, with 1075 (40%) being obstetric patients. After program implementation, significant improvements were seen in each of the IP areas: instrument decontamination, gown and drape integrity, surgical skin antisepsis, gauze counting, antibiotic administration, and use of the surgical safety checklist. At baseline, unadjusted SSI rate was 11.3% overall and 12.4% for the obstetric group; after Clean Cut implementation, the SSI rate fell to 6.2% overall and 6.6% in the obstetric group (a 47% decrease).

---

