### 1.1. Measurement of compliance

Each of the six domains of perioperative infection prevention include two or more related behaviors. The result of each domain is measured as a binary, where 1 = all behaviors in the domain were performed during the procedure, and 0 = at least one of the behaviors was not performed.

To capture overall compliance, we will construct a “high compliance” flag where:

1 = 5 or 6 domains were performed in the surgery

0 = 0 to 4 domains were performed in the surgery

We based this cut point between 4 and 5 on the global distribution of compliance scores. This cut point roughly splits the cases: about half were high compliance, half were not.

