### 1.2. Multiple comparisons

This analysis includes 6 aims, which collectively involve fitting 12 models (Table 7). Each model has a single predictor of interest, which is the intervention variable in all models except in aim 6, where the predictor of interest is the flag for high-compliance surgeries. We will evaluate each p value against an alpha of 0.05 and will not adjust for multiplicity.

Table 7: Number of planned models across all aims

|            |       |                                                | N models |
|------------|-------|------------------------------------------------|----------|
| Primary    | Aim 1 | Infection reduction in CS                      | 1        |
| Secondary  | Aim 2 | 6 compliance domains, 1 overall score          | 7        |
|            | Aim 3 | Reduced maternal postoperative mortality       | 1        |
|            | Aim 4 | Reduced neonatal mortality                     | 1        |
| Additional | Aim 5 | SSI, maternal mortality, or neonatal mortality | 1        |
|            | Aim 6 | Compliance, surgical infection                 | 1        |

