### 9.4 Sensitivity to choice of model

In our primary analysis (aim 1), we will use mixed effects logistic regression, fitting random intercepts for each of the five cohorts, which are defined in tables 2 and 3 above. This accounts for our hierarchical data with a random effect, so we will interpret the resulting ORs as the estimated effect of CLEAN-CUT implementation on the individual patient level (known as subject-specific or conditional estimates). An example interpretive sentence might be: “In our study, individuals who underwent a CS after CLEAN-CUT implementation were X% less likely to develop an SSI.”

In this sensitivity analysis of our primary aim, we will use a generalized estimating equation (GEE) framework with the same data. One strength of GEE is its accommodation of repeated measures of individual patients over time. While we do not measure patients repeatedly in our study, one view of our data is that the operating theater and team are measured repeatedly over time. Under this view, we will treat cohort as the unit of repeated measure in the GEE, using an autoregressive covariance structure, which assumes the strongest correlations between adjacent time periods and systematically decreasing correlations with increasing distance in time.

This accounts for our hierarchical data with repeated measures, so we will interpret the resulting ORs as the estimated effect of Clean Cut implementation on the population level (known as marginal effects). An example interpretive sentence might be: “For the hospitals in our study, the population of CS patients was X% less likely to develop an SSI after the implementation of Clean Cut.”

The difference in interpretation between ME and GEE is fairly subtle, and in most applications their estimates are similar. In the event that the magnitude or significance of the OR differs in our data between these models, then we will investigate further the pattern and magnitude of clustering effects to identify the cause of the differences.

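### The low-baseline-risk reason for reporting only odds ratios does not fit the compliance outcomes, at least the high-compliance flag, and the SSI example sentences read an odds ratio as a risk ratio

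*Combined protocol and SAP*

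**What the plan says.** SAP 7.1 sets one mixed-effects logistic model for the analysis. Its estimate of interest is the exponentiated intervention coefficient, "which will express the odds ratio (OR) of having the outcome after the intervention started versus beforehand". A note recalls that in the pilot "we modeled the surgical infection outcome with a modified Poisson regression", which gives relative risks directly, and accepts that odds ratios can overstate relative risks when the baseline risk is high. It then sets the point aside: "in this case we believe the baseline risks are low enough as to not require this correction". Its second reason is that the trial will keep the standard logistic mixed model for stepped-wedge trials.

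On the number of models, the Multiple comparisons section states: "This analysis includes 6 aims, which collectively involve fitting 12 models". Table 7 gives Aim 2 seven of them: "6 compliance domains, 1 overall score". SAP 8.3 builds these by making each compliance binary the dependent variable and dropping the demographic covariates. It promises percentages by condition for the six domains and draws its conclusion from the direction and significance of the odds ratio. A last model uses the high-compliance flag (5 or 6 domains met). The Measurement of compliance section says of that cut point: "about half were high compliance, half were not".

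SAP 9.4 (choice of model) explains how the odds ratios for SSI will be read. Its mixed-model example is "individuals who underwent a CS after CLEAN-CUT implementation were X% less likely to develop an SSI", and the GEE example uses the same kind of wording for the population of patients.

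**The concern.** The low-risk reason stands in the general modelling section, so it covers all twelve models as written. Seven of those have compliance as the outcome, and for at least one of them the outcome is common by construction. For a common outcome the odds ratio lies well away from the risk ratio, and a reader who takes one for the other will think that compliance changed more than it did.

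The promised percentages help only in part. They cover the six domains but not the flag. They are also crude, while condition is tied to calendar time in a stepped wedge, which is why the model carries 18 month levels. The odds ratio is therefore the only adjusted measure of effect size planned for any compliance outcome.

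The example sentences raise a smaller, separate problem on the primary outcome: they attach risk wording to an odds ratio.

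**Working it through.** **Model count.** Table 7: 1 + 7 + 1 + 1 + 1 + 1 = 12, which agrees with the SAP; 7 of the 12 have a compliance outcome. The SAP gives no odds ratio, risk ratio or domain rate to reproduce.

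**Formulas.** With p0 the control proportion and p1 the intervention proportion:
- RR = p1/p0
- OR = p1(1 − p0) / [p0(1 − p1)]
- (OR − 1)/(RR − 1) = 1/(1 − p1), the factor by which the excess over 1 is inflated if the OR is read as an RR.

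**High-compliance flag.** Inputs:
- about 50% of cases meet it (Measurement of compliance), taken as pooled over conditions because the SAP does not split it;
- control share 5,715/10,666 = 0.536 and intervention share 4,951/10,666 = 0.464 (SAP Table 2);
- a rise of d between conditions, which the documents do not give, assumed here to be 10 to 30 points.

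Then p0 = 0.50 − 0.464d and p1 = p0 + d.

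| Assumed rise | p0 | p1 | RR | OR | (OR − 1)/(RR − 1) |
|---|---|---|---|---|---|
| 10 points | 0.454 | 0.554 | 1.22 | 1.49 | 2.2 |
| 20 points | 0.407 | 0.607 | 1.49 | 2.25 | 2.5 |
| 30 points | 0.361 | 0.661 | 1.83 | 3.45 | 3.0 |

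**Six domains.** No rates are given. If half the cases meet 5 or 6 domains, the pooled mean domain rate lies between 41.7% (half the cases at 5 of 6, half at 0: 2.5/6) and 83.3% (half at 6, half at 4: 5/6). Single domains can lie outside that range, so no single distortion factor can be stated for them.

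**SSI.** Inputs are the protocol's power assumptions: 12% unexposed, with 8% and 9% exposed.
- 12% to 8%: RR = 0.08/0.12 = 0.667; OR = (0.08/0.92)/(0.12/0.88) = 0.638. A 36.2% reduction in odds against a 33.3% reduction in risk.
- 12% to 9%: RR = 0.09/0.12 = 0.750; OR = (0.09/0.91)/(0.12/0.88) = 0.725. A 27.5% reduction in odds against 25.0% in risk.

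These are crude figures. The model's odds ratios are conditional on month and cohort (and on covariates for SSI) and will differ somewhat.

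**The case against.** The strongest reply is that the low-risk sentence was meant for infection. The note opens with the pilot's infection model, and 7.1 codes the outcome as an adverse event, which compliance is not. That reading is fair, but the text does not state it, and 8.3 uses the same model for compliance without comment.

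The second reason, staying with the standard stepped-wedge model, does not depend on baseline risk. It stands, and it supports keeping the logistic model for the test. It is no reason to leave out a risk-scale summary from that fit.

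Aim 2 is also partly protected: its conclusions rest on direction and significance, the six domains get percentages, and no risk wording is planned for compliance. All of this stands. The SSI wording is offered only as an example, and its distortion is small.

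A reader might go further in several ways that the documents do not support:
- **All seven compliance outcomes are near 50%.** Only the flag is documented there, and that rate is not a baseline rate.
- **The pilot fixes the size.** The protocol says "At baseline, perioperative teams only complied with an average of 2.9 of the six critical perioperative infection prevention standards", rising to 4.5. Treating 2.9/6 and 4.5/6 as probabilities gives RR 1.55 and OR 3.21, but a mean score is not the probability of any one planned binary outcome.
- **Comparison with the pilot's compliance relative risks is lost.** The protocol reports none. Pilot compliance is given as mean scores, and both pilot relative risks are for infection.

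**Conclusion.** The point holds as a matter of reporting. The low-risk reason is tolerable for SSI, where the odds ratio overstates the relative reduction by about 2 to 3 percentage points, and for deaths, which the SAP expects to be rare. It fails for the high-compliance flag, where the excess over 1 would look 2.2 to 3.0 times too large if the odds ratio were read as a risk ratio. That size rests on the pooled 50% figure, on the enrolment split applying to the intraoperative population, and on the assumed rise of 10 to 30 points. For the six domains the size is unknown.

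It would be wrong to infer that the SAP sets out to report compliance odds ratios as risks: it names them as odds ratios, and risk wording appears only for SSI. It would also be wrong to infer that any test, p-value or decision rule is affected. What is open to misreading is the size of the compliance effect and, slightly, of the SSI effect.

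**What to change.** 1. In 7.1, limit the low-baseline-risk sentence to SSI and mortality, and say that compliance odds ratios are not to be read as risk ratios.
2. Keep the mixed logistic model for all tests.
3. For the seven compliance models and the primary SSI model, also report standardised (marginal) risk differences, risk ratios or both, with confidence intervals from the same fit. State how the cohort effect is handled in the averaging.
4. In 8.3, add the flag's percentage by condition to those promised for the six domains.
5. In both example sentences of 9.4 (choice of model), keep the percent-less-likely wording for a risk ratio only; for an odds ratio, write X% lower odds.

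The cost is SAP wording and a small post-estimation step, with no new data. There is no need to return to the pilot's modified Poisson model: it relies on robust errors, which would be fragile with five cohorts.
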